## Abstract

**Background:**

Depression and anxiety are common problems among breast cancer survivors. Carer support is one of the most important determinants of women's psychological wellbeing. Survivors' distress can be alleviated by giving carers access to survivors' evidence-based treatment, which will help carers understand what survivors have been going through and help survivors feel more supported. Given the limited access to evidence-based treatments, an adapted internet-delivered cognitive behavioural therapy (iCBT) intervention for breast cancer survivors, but also open for carers' access, has the potential to decrease survivors' depression and anxiety symptoms and improve cancer-related communication and relationship quality between survivors and carers.

**Objectives:**

This study evaluates (1) the effectiveness of a guided iCBT intervention for depression and/or anxiety symptoms among breast cancer survivors with and without main carer access, and (2) the acceptability and satisfaction with the iCBT programme.

**Method:**

In this pilot study comparing the effectiveness of an adapted 7-week iCBT without main carer access against the iCBT with main carer access and treatment-as-usual control, 108 breast cancer survivors will be recruited and then randomised to either (1) treatment (*n* = 72) or (2) treatment-as-usual control group (*n* = 36) with a 2:1 ratio. The participants in the treatment group will be assigned to either iCBT alone or iCBT with the main carer also having access to the same content based on their preference. The primary outcome measure is the Hospital Anxiety and Depression Scale, and alongside secondary measures such as Cancer-Related Quality of Life, Breast Cancer Worry Scale, Brief COPE, and Medical Outcomes Study Social Support Survey will be completed by the survivors at baseline, post-treatment, and 2-month follow-up. Survivors who have carers will also complete Survivor-Carer Cancer Communication and Relationship Quality measures to provide insights into the effects of carer access. To assess the acceptability and satisfaction with the programme, survivors and their main carers will fill out the Helpful Aspects of Therapy Form (HAT) and Satisfaction with Online Treatment (SAT). Programme effectiveness and the effects of carer access on primary and secondary outcome measures will be evaluated on intention-to-treat and per-protocol basis using Linear-Mixed-Models.

**Discussion:**

This is the first trial comparing the effectiveness and acceptability of iCBT with and without carer access for depression and anxiety among breast cancer survivors. The findings of this study will provide novel data on the acceptability of iCBT programmes for breast cancer survivors and the impact of carer access on them and their carers.

## Background

1

Improvements in the early detection and treatment of cancer have resulted in an increasing number of people living with cancer for longer periods (Niedzwiedz et al., 2019; Simard and Savard, 2009). Research shows that clinical levels of depression and anxiety are common problems among people as they adjust to the illness (Baqutayan, 2012; Croyle and Rowland, 2003; Fann et al., 2008; Hopko et al., 2016b; Puigpinós-Riera et al., 2018; Reich et al., 2008; Spiegel and Riba, 2015), and symptoms of distress remain for some patients 20 years after the initial treatment (Hegel et al., 2006). Depression and anxiety symptoms in people living with breast cancer are associated with poorer physical health, more pain and fatigue, more substance use, poorer quality of life, less acceptance and compliance with adjuvant treatments, higher prevalence of metastasis, higher risk of relapse and mortality, as well as lower survival time (Chida et al., 2008; Colleoni et al., 2000; Hjerl et al., 2003; Hopko et al., 2008; Hopko et al., 2014; Hopko et al., 2016a; Reich et al., 2008; Reuter et al., 2006; Reyes-Gibby et al., 2012; Somerset et al., 2004; Spiegel and Riba, 2015). Therefore, treating the distress associated with the illness is of critical importance.

Women with breast cancer often deal with this stressful experience by turning to their partners or spouses (Manne et al., 2016; Salakari et al., 2017), or their close relatives, and friends for emotional support (Ockerby et al., 2013); usually one of these people will assume a caregiver role (Tiete et al., 2020). Social support from significant others is one of the most important determinants of patients' positive psychological adjustment and lower psychological distress (Helgeson et al., 2004; Hughes et al., 2014; Ng et al., 2015; Thompson et al., 2017). Open and mutual communication about cancer-related issues and concerns between patients and carers has been associated with less distress and greater relationship satisfaction for both patients and their partners (Manne et al., 2006). A recent randomised controlled study suggested that encouraging cancer patients and carers to express their personal cancer-related concerns helps improve their coping ability with the illness (Tiete et al., 2020). Active participation of the carer in the intervention through a couple-based intervention might help improve the quality of life, psychological distress, and relationship functioning of couples coping with breast cancer as demonstrated by a systematic review (Brandão et al., 2014). However, couple-based interventions for cancer have lower uptake rates than individual-based interventions, especially when both the patient and the carer are required to participate in the intervention simultaneously (Hopkinson et al., 2012; Regan et al., 2013).

Several meta-analyses have established Cognitive Behavioural Therapy (CBT) as clinically effective in the treatment of depression and anxiety among breast cancer patients and survivors (Tatrow and Montgomery, 2006; Xiao et al., 2017; Ye et al., 2018). Its long-term effect on reducing depression and increasing quality of life among breast cancer survivors was also shown in a randomised controlled trial with an 11-year follow-up (Stagl et al., 2015). A CBT intervention teaching adaptive coping skills to manage daily stressors and encourage the use of social resources reduced depression levels among women with breast cancer (Gudenkauf et al., 2015). Consistent with this finding, studies with breast cancer patients revealed that active coping strategies were associated with better adjustment and quality of life, whereas avoidant coping strategies were associated with poorer psychological well-being and decreased quality of life (Holland and Holahan, 2003; Kershaw et al., 2004; Moorey and Greer, 2012).

However, access to evidence-based CBT treatments remains challenging (Etzelmueller et al., 2018) due to the costs, distance to service locations, perceived personal stigma of mental disorders and treatments, lack of trained therapists, inadequate treatment, and delayed treatment provision (Kessler et al., 2001; Mohr et al., 2010; Wang et al., 2007; Wittchen et al., 2011). Besides, many people living with cancer who could benefit from psychological support remain untreated because of the under-recognition of the need for psychosocial care by their primary oncology team (Fallowfield et al., 2001) and even when recognised, the lack of professionals to provide psychological support to cancer patients is hindering (Jacobsen and Jim, 2008).

An internet-delivered cognitive behavioural therapy (iCBT) intervention focusing mainly on alleviating survivors' depression and anxiety symptoms, but also open for carers (e.g., spouses, family members, and friends) to access may overcome these aforementioned challenges. It would allow breast cancer survivors and their carers access to the programme at a time and place convenient to them regardless of their location; furthermore, it may reduce concerns about stigma and privacy (Andersson and Titov, 2014; Donker et al., 2015; Griffiths and Christensen, 2007). Giving carers access to the iCBT content, which does not require simultaneous log-in by survivors and their informal carers might be more appealing for this population, considering carers' difficulty to find time due to other commitments (Regan et al., 2013). Carer access would help carers to better understand what survivors have been going through and widen their knowledge about cancer-related issues from the survivors' perspective. Having the same knowledge through accessing to same content may also encourage them to openly discuss their cancer-related concerns and practice the coping skills that they learned together to deal with psychological distress. This may improve survivors' perceived social support, cancer-related communication, and relationship quality between survivors and carers; this may result in a further decrease in survivors' depression and anxiety symptoms in combination with the treatment effect.

### Effectiveness of iCBT in the treatment of depression and anxiety in breast cancer

1.1

iCBT is a promising approach that can be used to provide information and support to cancer survivors on managing unhelpful thinking and behaviours, normalising feelings, and thereby relieving distress (Igelström et al., 2020). Research shows that iCBT interventions are highly effective in the treatment of major depression (Andersson and Cuijpers, 2009; Hedman et al., 2012; Wright et al., 2019), subthreshold depression (Buntrock et al., 2015; Spek et al., 2007b), anxiety (Richards and Richardson, 2012; Spek et al., 2007a; Titov et al., 2009), as well as for comorbid depression and anxiety (Newby et al., 2013) in the general population. In a meta-analysis, guided self-help and face-to-face therapy for depression and anxiety disorders had comparable effect sizes at post-treatment and follow-up periods for up to 1 year, suggesting no statistically significant differences (Cuijpers et al., 2010). Guided iCBT interventions (supported by coach or therapist) for depression and anxiety have been found as more cost-effective than waiting-list, treatment-as-usual, attention-control, telephone counselling, group cognitive behaviour therapy, and unguided internet CBT (Donker et al., 2015; McCrone et al., 2004).

Effectiveness studies of iCBT interventions for depression and anxiety among cancer patients and survivors are only recently emerging, and most studies have included people with all cancer types rather than focusing only on one type of cancer (e.g. Beatty et al., 2016; Duffecey et al., 2013; Murphy et al., 2019; Willems et al., 2017). A randomised controlled trial provided support for the short-term effectiveness of an online intervention that teaches skills to manage psychosocial and lifestyle-related issues in reducing depression and fatigue among cancer survivors (Willems et al., 2017). Similarly, a randomised controlled trial of iCBT for clinical depression and/or anxiety revealed that cancer survivors in the iCBT group showed significant reductions in anxiety and depression symptoms, general distress, fear of cancer recurrence, and significantly higher quality of life at post-treatment compared to the survivors receiving treatment-as-usual (Murphy et al., 2019). A recent review of online interventions (including web-based, blended care, telehealth, mHealth, and other online interventions) aimed at reducing psychological distress in cancer patients demonstrated mixed findings (Willems et al., 2020). The findings partially supported the reduction of psychological distress and depression following the intervention; however, the evidence for reducing anxiety was limited. Given the limited number of studies, more studies and larger effectiveness trials are needed.

In qualitative research, iCBT has also been demonstrated as acceptable among cancer patients who used the programme. Early-stage cancer patients and survivors with depression and/or anxiety found the iCBT programme acceptable in terms of the format of internet-delivery and the user-friendly nature of the material; overall, participants had good engagement with the programme (Karageorge et al., 2017). Both recent cancer survivors and providers working in cancer care in Canada reported that therapist-guided iCBT is acceptable for their needs (Alberts et al., 2018). Likewise, cancer patients (breast, colorectal, and prostate) undergoing cancer treatment and concurrently experiencing depression and/or anxiety symptoms found it beneficial to have direct access to the online intervention programme as they have been experiencing time constraints in everyday life (Igelström et al., 2020). However, no study has investigated the attitudes of breast cancer survivors and/or their main carers toward iCBT programmes.

Internet interventions designed specifically for people living with breast cancer have so far focused on insomnia (Dozeman et al., 2017; Zachariae et al., 2018), sexual dysfunction (Hummel et al., 2015), body image (Hummel et al., 2018), treatment-induced menopausal symptoms (Atema et al., 2019; Atema et al., 2016), and fatigue (Abrahams et al., 2017). The number of iCBT studies targeting the symptoms of depression and anxiety in people living with breast cancer is indeed very limited (Carpenter et al., 2014; Owen et al., 2005) and the available interventions were self-guided, i.e., no supporter or therapist provided feedback to the users on the programme. However, the findings of the available studies demonstrated promising results. For example, Carpenter et al. (2014) found that 10-week self-guided iCBT is effective in improving self-efficacy for coping with cancer, regulating negative mood, and lower levels of cancer-related post-traumatic stress symptoms compared to the control group among breast cancer patients. Owen et al. (2005) examined the effects of a self-guided internet coping group among women living with early-stage breast cancer in a randomised pilot study and found that women with low self-reported health status at baseline had greater improvement in their perceived overall health after the treatment. However, to the best of our knowledge, there is no available guided internet intervention aiming to alleviate depression and anxiety symptoms specifically in breast cancer survivors.

Despite the critical influence of the social environment, specifically the perceptions of partner and carer support, on breast cancer patients' psychological adjustment (Gremore et al., 2011; Helgeson and Cohen, 1996; Manne et al., 2014; Manne et al., 2005; Sormanti and Kayser, 2000), only one randomised controlled trial included male partners of young women with breast cancer in an online intervention with a couple-based approach; no findings have been published yet (Fergus et al., 2015). To date, no trial on internet interventions has evaluated whether giving main carers access to the breast cancer survivors' programme has any effect and whether giving carers access decreases survivors' psychological distress further. There are some internet interventions available for caregivers of different populations such as the caregivers of women with breast cancer (Levesque et al., 2018), depressed patients (Blom et al., 2015; Bijker et al., 2017), and people with dementia (Meichsner et al., 2019). However, none of these studies targeted breast cancer survivors' well-being or psychological distress but focused only on improving caregivers' well-being.

### Adaptation of the iCBT programme for breast cancer survivors

1.2

Space from Depression and Anxiety is an 8-week CBT based online intervention programme, designed originally for the treatment of depression and anxiety symptoms in the general population and adapted for the breast cancer context for this study. The original Space from Depression programme (without the anxiety module) has been found effective for adults with depressive symptoms in the general population, with a large effect size at post-treatment (d = 0.91; Richards et al., 2015). The differences between treatment and waiting-list control group also yielded statistically significant results, with a moderate to large effect size (d = 0.50), and these improvements on the outcomes were maintained at 6-month follow-up. Most participants reported that they were satisfied with the programme, felt supported, reported positive gains and impact, and perceived these as lasting effects (Richards et al., 2016). However, the programme content (e.g., examples and personal stories) was not suitable for the breast cancer survivor and carer context, thus adaptation was required. In a recent randomised waitlist-controlled effectiveness and cost-effectiveness trial of digital interventions, it was found that 8-week iCBT for depression and anxiety is not only effective but also potentially cost-effective in the long-term within the improving access to psychological therapies programme (IAPT) in the UK (Richards et al., 2020).

### Space in breast cancer from depression and anxiety

1.3

For the adaptation of the programme, *Space in Breast Cancer from Depression and Anxiety*, semi-structured interviews were conducted with 5 women living with breast cancer and 3 main carers (sister, partner, friend). Based on their feedback on the original programme and the findings in the literature, the programme has been adapted for women with breast cancer and their main carers by the principal researcher [name]. After the adaptation of the content, one woman living with breast cancer, who completed the treatment, evaluated all the personal stories, and stories were tailored accordingly. Then, a clinical psychologist, who is an expert in CBT and psycho-oncology reviewed the first three modules of the adapted programme and gave feedback. Next, the primary researcher reviewed the changes and edited the whole programme content based on the received feedback. Afterward, another clinical psychologist who is an expert in CBT reviewed the adapted content including all eight modules and the programme content was updated accordingly.

The adaptation included combining the first two modules, updating and checking the relevance of research-based information in the breast cancer context, adding information on (i) breast cancer (definition, risk factors, its effects on well-being), (ii) the manifestation of depression and anxiety symptoms in breast cancer, (iii) the effectiveness and use of CBT for breast cancer, (iv) adapting physical activities for patients who have finished their treatment, and (v) how to support as a carer. Furthermore, the quiz questions and answers were revised to make them focused on the module content.

The personal stories in the programme were rewritten for breast cancer survivors, which were mostly inspired by the experiences of the interview participants and the clinical knowledge of the primary researcher. This was done to help survivors and carers relate to personal stories. In total 6 personal stories were prepared: 2 representing single women living with breast cancer, 2 for informal carers of the survivors, and 2 for survivor-carer cancer-related relationship problems. Careful attention was paid to ensure that the stories accurately portrayed different experiences. As the fear of cancer returning and progressing in the same organ or another part of the body is one of the most common and distressing concerns among cancer survivors (Niedzwiedz et al., 2019; Simard and Savard, 2009; Yang et al., 2019), the fear of recurrence was also captured in the stories in addition to the examples in other sections of the programme. Photos in the personal stories section of each module were also replaced with images that best suited the new characters created.

Moreover, all the examples were checked and replaced with breast-cancer specific examples in sections such as thinking errors, thoughts-feelings-behaviour (TFB) cycles, and worry cycles. For example, the TFB cycle examples did not address the common negative thoughts experienced by breast cancer patients; thus, they were changed with the ones such as “I can't cope with breast cancer” or “My cancer will come back”. Furthermore, there were other examples in the programme that did not fit the new context. For example, an example of catastrophising in the thinking errors section was “Stumbling over a few words when giving a presentation and then thinking the whole thing was a mess”, which did not match the new context; therefore, these were modified, for example, with “although your doctor says your prognosis is good, you still believe that you can't recover from cancer” to reflect common thinking patterns in the context of breast cancer.

Information on fatigue was added as suggested by the patients in Alberts et al.'s study (2018). Information on emotional expression and effective listening was also added as it was the main difficulty mentioned by most of the participants during the interviews and was not included in the original version of the programme. In addition, distraction techniques for coping with difficult situations were introduced in the Challenging Thoughts module as some of the negative thoughts that patients with advanced breast cancer experience (e.g., the possibility of treatment failure, the possibility of death) may indeed have a realistic basis (Moorey and Greer, 2012). Content that is suitable for breast cancer patients was kept as it is.

### Aims of the study

1.4

The present pilot study has six aims:a)To evaluate the effectiveness of an adapted iCBT on the treatment of breast cancer survivors' depression and anxiety symptoms in response to the treatmentb)To determine any changes in breast cancer survivors' quality of life, coping, fear of cancer recurrence in response to the treatmentc)To evaluate any changes in breast cancer survivors' perceived social support, cancer communication, and relationship quality in response to the carer access to survivors' treatment contentd)To evaluate any changes in carers' cancer communication and relationship quality in response to their access to survivors' treatment contente)To compare the effects of an adapted iCBT with and without main carer access on breast cancer survivors' depression and anxiety symptomsf)To evaluate the helpful aspects of the iCBT intervention and satisfaction with the programme among breast cancer survivors and their main carers

Therefore, breast cancer survivors will be randomly assigned to either iCBT intervention or treatment-as-usual control. The survivors assigned to the iCBT intervention group and who have a carer will be asked their preference to give their carers access to the intervention programme content. The iCBT group will be allocated to either iCBT alone or iCBT with carer access based on their preference. Therefore, there will be 3 groups in total.

Group 1: iCBT alone

Group 2: iCBT with carer access

Group 3: Treatment-as-usual control

### Hypotheses and research questions

1.5

Hypothesis about the primary outcomes:**H1**Survivors in both treatment groups (Group 1 and Group 2) are expected to show a greater reduction in depression and anxiety symptoms than survivors in the TAU (Group 3) at post-treatment and 2-month follow-up.

Hypotheses about the secondary outcomes:**H2**Survivors in both treatment groups (Group 1 and Group 2) are expected to have greater improvements in cancer-related quality of life, coping, and fear of recurrence compared to survivors in the TAU (Group 3) at post-treatment and 2-month follow-up.**H3**Survivors in both treatment groups (Group 1 and Group 2) are expected to use more active coping strategies than survivors in the TAU (Group 3) at post-treatment and 2-month follow-up.**H4**A reduction in depression and anxiety symptoms of survivors in both treatment groups (Group 1 and Group 2) is expected to be mediated by the change in coping strategies after controlling for depression and anxiety levels at baseline.**H5**An improvement in cancer-related quality of life in both treatment groups (Group 1 and Group 2) will be mediated by the change in coping strategies after controlling for cancer-related quality of life at baseline.

The effects of carer access will be explored using the following research questions:

**RQ1.** Is there a difference in depression and anxiety scores between iCBT alone (Group 1) and iCBT with the carer access (Group 2) at post-treatment after controlling for baseline depression and anxiety scores?

**RQ2.** Is there a difference in perceived social support between iCBT alone (Group 1) and iCBT with the carer access (Group 2) at post-treatment after controlling for baseline perceived social support?

**RQ3.** Is there a difference in survivor-carer relationship outcomes (cancer-related communication quality and relationship quality) of survivors in iCBT with carer access between baseline and post-treatment?

**RQ4.** Is there a difference in survivor-carer relationship outcomes (cancer-related communication quality and survivor-carer relationship quality) of carers between baseline and post-treatment?

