### Randomisation

2.5

Eligible participants will be randomly assigned to either iCBT intervention (n = 72) or treatment-as-usual control (*n* = 36) with a 2:1 ratio. Those who are assigned to iCBT group and have carers will be asked whether they will participate with or without their main carer. Participants will be assigned to iCBT alone or iCBT with carer access based on their preference and informed immediately about their group assignment. Survivors in the iCBT alone group (Group 1) will be using the iCBT programme by themselves, and survivors in the iCBT with the main carer access group (Group 2) will be using the same programme, but their main carers will also have access to the programme content using a separate username and password. Participants in the treatment-as-usual control group (Group 3) will continue their usual care and will not receive the iCBT programme during this study. They will fill out the same measures as the other two groups at pre-treatment, post-treatment, and 2-month follow-up.

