### Procedure

2.6

The link on the advertisement will direct potential participants to a Qualtrics page to complete the informed consent, screening questionnaire assessing inclusion criteria, demographic information, and health status. All participants will be responsible for self-screening as their eligibility will be determined based on their responses to the questions set-up in Qualtrics. The survey is designed to automatically exclude respondents who select “yes” to the questions asking current suicidal ideation or intent, current alcohol or drug misuse, and organic mental health condition (such as schizophrenia, psychosis, and bipolar disorder), and current psychotherapy for depression or anxiety. Potential participants who responded yes to the questions regarding current suicidal ideation and intent will see a message providing contact details for recommended support services on the screen. Eligible survivors will be able to continue with baseline questionnaires (Time 1) assessing depression and anxiety symptoms, quality of life, fear of recurrence, coping, perceived social support, relationship quality, and cancer-related communication. After filling out the questionnaires, eligible participants will be automatically randomised and those who prefer to participate with their carer (iCBT with the main carer access) will be asked to provide their carers' email address on the Qualtrics page. Carers will be contacted through the email address provided by breast cancer survivors and asked to complete the informed consent, screening questionnaire, and survivor-carer cancer communication, and relationship quality measures through a separate Qualtrics link. All survivors and carers will be reassessed online at the end of the intervention (7 weeks after they started, Time 2), and at 2-month follow-up (Time 3). At the end of the intervention, survivors and their main carers in both treatment groups will be asked about their perspectives on the helpful aspects of the programme and their satisfaction with the programme.

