##### Brief coping orientation to problems encountered (brief COPE) inventory

2.9.3.3

The Brief COPE is a 28-item measure, which assesses strategies used for coping with a stressful life event (Carver, 1997). This inventory is an abbreviated version of the full 60-item COPE Inventory (Carver et al., 1989) and assesses 14 different coping strategies: self-distraction, active coping, denial, substance use, emotional support, instrumental support, behavioural disengagement, venting, positive reframing, planning, humour, acceptance, religion, and self-blame (Carver, 1997). It has response options range from (1) I haven't been doing this at all to (4) I have been doing this a lot. It measures both adaptive and maladaptive coping strategies and is commonly used for measuring coping with health-related conditions (Rand et al., 2019). In the present study, the instructions were modified to ask how participants had been coping with breast cancer-related stress in their life. Item samples are: “I've been turning to work or other activities to take my mind off things”, “I've been concentrating my efforts on doing something about the situation I'm in”. This scale will be used to measure potential changes in survivors' ways of coping with stress related to breast cancer before and after the intervention. The Brief COPE has been demonstrated to be reasonably reliable with Cronbach alpha levels ranging from 0.50 to 0.90 for each subscale (Carver, 1997; Rand et al., 2019). In the present study, instead of 14 subscales, 2 coping dimensions that assess efforts to move toward goals (active coping) and to disengage from goal pursuits (avoidant coping) will be used (Kershaw et al., 2004; Rand et al., 2019).

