Mediation analyses using PROCESS for SPSS (Hayes, 2013; Hayes and Rockwood, 2017) will be used to test the role of change in coping strategies following the iCBT treatment on survivors' outcomes such as depression and anxiety scores and cancer-related quality of life. The estimates of indirect effects will be generated using the bootstrapping method (*n* = 5000 bootstrap re-samples) and a 95% confidence interval (Preacher and Hayes, 2008). If the 95% confidence interval does not include the value of zero, this supports a claim of mediation, i.e., the effect of the independent variable on the outcome variable is contingent upon the effect of the proposed mediator. The bootstrapping method was preferred over the Sobel test as it does not impose the assumption of normality of the sampling distribution and the sampling distribution of the indirect effect is frequently non-normal.

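### H4 and H5 make change in coping the mediator but name no baseline coping covariate; with a raw difference score, the coping-to-outcome path can be biased, mainly towards missing true mediation

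*Protocol article*

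**What the plan says.** In the protocol article, section 1.5 (Hypotheses and research questions), H4 states that the reduction in depression and anxiety "is expected to be mediated by the change in coping strategies after controlling for depression and anxiety levels at baseline". H5 states that the gain in quality of life "will be mediated by the change in coping strategies after controlling for cancer-related quality of life at baseline". In both, the mediator is change in coping, and the only covariate named is the baseline value of the outcome.

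Section 2.10.2 gives the method, "Mediation analyses using PROCESS for SPSS", with 5000 bootstrap resamples, and the reading rule: "If the 95% confidence interval does not include the value of zero, this supports a claim of mediation". It lists no covariates and gives no formula for change. It does not say whether the independent variable is randomised iCBT versus TAU or the three groups.

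On the mediator, section 2.9.3.3 says that "2 coping dimensions that assess efforts to move toward goals (active coping) and to disengage from goal pursuits (avoidant coping) will be used". Section 2.6 (Procedure) shows that coping is measured before randomisation: "Eligible survivors will be able to continue with baseline questionnaires (Time 1) assessing depression and anxiety symptoms, quality of life, fear of recurrence, coping". By contrast, RQ1 and RQ2 in section 1.5 and the carer analyses in section 2.10.3 do plan control for a measure's own baseline.

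**The concern.** A difference score contains baseline coping with a negative sign. If baseline coping is not in the outcome model, the coefficient on the difference blends the effect of coping after treatment with the sign-reversed effect of coping before it. The product of paths that is bootstrapped inherits that bias.

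The protocol's background (section 1) links use of active coping to better adjustment and avoidant coping to poorer well-being. That describes levels of coping, which is the situation in which the omission does harm.

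H4 and H5 are the trial's only hypotheses about mechanism. The Discussion calls the trial adequately powered for its secondary hypotheses, and these two are among them.

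**Working it through.** **The plan's own figures.** The sample size is set for HADS-T with f = 0.30, not for mediation. The attrition step reproduces: 81/(1 - 0.25) = 108, 54/0.75 = 72, 27/0.75 = 36. No power or effect size is given for H4 or H5, so N = 81 and N = 108 serve as the range of analysable numbers.

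**Assumed inputs (none is in the documents; SD units).** Coping has SD 1 within arm at both times. Stability s = 0.6 (range 0.5 to 0.7). Baseline coping correlates -0.4 with the baseline outcome. Path a (iCBT to coping) = 0.5. Path b (coping to outcome) = -0.4 or 0. The direct effect d of baseline coping on the later outcome runs from -0.3 to +0.4.

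**Model.** M1 = s·M0 + a·T + e, with Var(e) = 1 - s². Y1 depends on Y0, T, b·M1 and d·M0. The mediator as literally worded is C = M1 - M0.

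**Path a without baseline coping.** The arm difference in C is (s - 1) × (arm difference in M0) + a. Randomisation makes the first term zero in expectation. Simulation agreed: 0.50 for a true 0.50, and 0.00 for a true 0.

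**Path b without baseline coping.** Given T and Y0, Var(M0) = 1 - 0.4² = 0.84. Then:
- Var(C) = (s - 1)² × 0.84 + (1 - s²) = 0.1344 + 0.64 = 0.7744
- Cov(C, M1) = (s - 1) × s × 0.84 + (1 - s²) = -0.2016 + 0.64 = 0.4384
- Cov(C, M0) = (s - 1) × 0.84 = -0.336
- Fitted b = b × 0.4384/0.7744 + d × (-0.336/0.7744) = 0.566·b - 0.434·d

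Putting in values:
- Level of coping matters (b = -0.4, d = 0): fitted b = -0.226; indirect effect 0.5 × -0.226 = -0.113 instead of -0.200, which is 43% too small. At s = 0.5 the ratio is 0.54/0.96 = 0.5625 (44% too small); at s = 0.7 it is 0.3336/0.5856 = 0.570 (43%).
- The same with d = -0.2: fitted b = -0.226 + 0.087 = -0.14; indirect effect -0.07.
- Only change matters (b = -0.4, d = +0.4): fitted b = -0.226 - 0.174 = -0.40, so no bias.
- No mediation, but baseline coping prognostic (b = 0, d = -0.3): fitted b = +0.13; indirect effect about +0.06, opposite in sign to H4.

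**Chance that the 95% percentile bootstrap interval excludes zero** (s = 0.6, 2:1 allocation, 1000 trials per setting, 500 resamples each rather than 5000; without v with baseline coping):

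| Setting | N = 81 | N = 108 |
|---|---|---|
| a = 0.5, b = -0.4, d = 0 | 32% v 67% | 52% v 83% |
| a = 0.5, b = -0.4, d = -0.2 | 14% v 72% | 20% v 85% |
| a = 0.5, b = -0.4, d = +0.4 (change causal) | 66% v 71% | 79% v 84% |
| a = 0.5, b = 0, d = -0.3 | 16% v 4% | 25% v 5% |
| a = 0.5, b = 0, d = 0 | 4.1% v 4.2% | 4.4% v 5.1% |
| a = 0, b = -0.4 | 2.4% v 6.1% | 3.4% v 6.3% |

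The simulation error of a 5% rate over 1000 trials is √(0.05 × 0.95/1000) = 0.7 points. In the first row, interval coverage at N = 81 is 75% without baseline coping and 93% with it.

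**Cross-check.** A second simulation (1500 trials per setting, Monte Carlo interval for the product, outcome = 0.5·Y0 + b·M1 + d·M0 - 0.3·T + error of SD 0.75) at 54 v 27 with the first row's settings gave 35/35/32% without and 65/70/74% with baseline coping, at stability 0.5/0.6/0.7.

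**The case against.** The strongest reply is that the omission is partly read from silence. Section 1.5 states hypotheses, not a model. Section 2.10.2 neither lists covariates nor says that the baseline outcome is the only one. Change could mean a residualised change, which is close to the remedy, and covariate lists are often left to an analysis plan. This stands as a limit: the point is conditional on a raw difference score. It does not remove the point, because the authors chose to name a covariate for the mediation hypotheses and the named set is insufficient under that reading.

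Second, H4 and H5 literally hypothesise that change mediates. If change is the causal quantity, nothing is biased. That stands too, but adjusting then costs nothing material, so the remedy is safe under either model.

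Three stronger readings are tempting and are not supported:
- A reader might infer that regression to the mean contaminates the estimated effect of iCBT on coping. Section 2.5 randomises iCBT against TAU, so that path is unbiased. The protection would be lost only if the preference-formed groups were the independent variable, which the article leaves open.
- A reader might infer that false claims of mediation are likely in general. They need three things together: iCBT truly changes coping, coping has no effect on outcome, and baseline coping predicts outcome beyond the baseline outcome. The other two null settings showed no inflation.
- A reader might infer that the plan would accept a wrong-sign effect as proof of H4. The hypotheses are directional, and the interval rule reads as a general gloss. The rule simply does not state a direction, and it should.

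**Conclusion.** The point holds in conditional form. As worded, with a raw difference score, H4 and H5 risk a biased coping-to-outcome path. The main consequence is missed mediation: an indirect effect about 43 to 44% too small, and roughly half the attainable power at N = 81, if the level of coping after treatment drives the outcome. False mediation, with the wrong sign, is the lesser and narrower risk (about 16% at N = 81 and 25% at N = 108 with a direct effect of -0.3).

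All sizes rest on assumed stability, correlations and path values, and on a single mediator; the documents supply none of these. H4 and H5 are secondary hypotheses in a pilot trial, and the primary HADS-T mixed model does not depend on them.

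**What to change.** In H4, H5 and section 2.10.2:
- Include the baseline value of each coping dimension used as a mediator, together with the baseline outcome, as covariates in both the mediator and the outcome equation. With baseline coping in both equations, the difference score and the Time 2 score give the same two path estimates, so the mediator may keep its name.
- Define the independent variable as randomised iCBT versus TAU.
- Count H4 or H5 as supported only if the interval excludes zero in the hypothesised direction.

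The cost is a sentence or two of wording and one or two covariates already collected at Time 1 (one per coping dimension in the model), with the same number of degrees of freedom in each equation. No new data are needed.
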